### 2.5. Inclusion criteria

In this study all children (boys and girls) aged between 3 and 12 years, who agree to participate in this study and have written informed consent forms signed by their representatives, will be included.

### 2.6. Exclusion criteria

Children who have endocrine diseases (juvenile diabetes, hyperlipidemia, and hypertension), diseases causing growth retardation (growth hormone deficiency due to pituitary disease), chromosomal abnormalities, or abnormal appearances will not be included in the study. Additionally, children who have not been born with a normal range of weight (i.e., they were less than 2.6 kg or > 4.4 kg), have received hormone replacement therapy, calcitonin, phosphonate, and growth hormone treatment within 6 months prior to the screening, or have any clinically significant acute or chronic diseases of the cardiovascular, endocrine, immune, respiratory, hepatobiliary, kidney, urological, neuropsychiatric, musculoskeletal, inflammatory, haemato-oncological, or gastrointestinal system, are not considered for participation. In this regard, children who have taken medicines or health functional foods related to children’s height growth or antipsychotics within three months prior to the study, as well as who have participated in another clinical trial within 1 month prior to the screening test, will be excluded from the study. Furthermore, any child who is determined as inappropriate for study due to other reasons, such as abnormalities in clinical laboratory tests, will be excluded from the trial.

### 2.7. Intervention

The intervention group will receive deer antler extracts (1,86 mg/20 mL) for 12 weeks. All participants would be instructed to administer the extracts once a day before theirs meals. Further, the children in the control group will receive a placebo with the same frequency using the same method.

### 2.8. Random assignment

During subject enrollment, the investigator will assign a unique identification code to each subject in the order of enrollment. Participants who meet the inclusion criteria will be assigned a randomized number according to the randomization plan. The randomization table is a sequential application of the permutations of random numbers (random numbers of A or B) generated by the random number generation program of the safety assessment set system, starting from subject number 1. This was designed and generated in advance by an independent statistician using safety assessment set V9.4 before clinical research. As children and adolescents in the growth and development stages are targeted, they will be divided into four stratified groups and randomly assigned to each group (Table 1).

**Table 1 T1:** Stratification of study subjects considering growth phase characteristics (gender and age)

Girls		Boys	
Group 1	Age between 3 and 9	Group 3	Age between 3 and 10
Group 2	Age between 9 and 12	Group 4	Age between 10 and 12

### 2.9. Outcome measurements

All data related to the measurements of outcome were directly entered into the an electronic case report file (e-CRF) by a clinical research coordinator who received appropriate training for clinical research.

#### 2.9..1. Primary outcome measurement.

Height will be measured using a portable stadiometer (Seca 213, Seca GmbH, Hamburg, Germany; measurement range: 20–205 cm) by a trained nurse at the same time of day with the participant barefoot, and the value will be rounded to 2 decimal places. Height and weight will be measured at baseline and at 6 and 12 weeks.

#### 2.9..2. Secondary *outcome measurement.*

##### 2.9..2..1. Weight and body mass index.

Weight will be measured while participants are in light clothing, using a load cell scale (CAS HE-30, Yangju, Republic of Korea; measuring range: 5–180 kg) by a trained nurse, and the value will be rounded to 2 decimal places. Body mass index will be calculated by dividing weight by the square of height.

##### 2.9..2..2. Percentile of height.

In this study, the height percentile will be measured at baseline and at 6 and 12 weeks. Accordingly, the recorded values will be interpreted using the growth chart of children and adolescents in Korea developed in 2017 to determine the growth status of participants.

##### 2.9..2..3. Waist and hip circumference.

Waist circumference and hip circumference will be measured three times (at baseline, and at 6 and 12 weeks) by the same researcher to prevent errors. Waist circumference will be measured in the middle between the lowest point of the ribs and the highest point of the pelvis according to the WHO standard. Hip circumference will be measured in a horizontal plane at the level of the maximum circumference of the hips and buttocks. Each value will be rounded to 2 decimal places.

##### 2.9..2..4. Bone age (BA) and predicted adult height (PAH).

BA and PAH will be measured at 6 and 12 weeks with VUNO Med BoneAge^TM^, an artificial intelligence program using the Greulich-Pyle (GP) method.

For unification of the analysis, for subjects whose PAH cannot be calculated with VUNO Med BoneAge^TM^ (chronologic age 4 years or older and bone age 7 years or less; bone age and chronological age are more than 2 years apart), PAH will be calculated using the Tanner–Whitehouse (TW) method. Furthermore, in case of 3 years old children for whom the PAH cannot be calculated even with the TW method, the predicted height will be calculated using a growth chart.

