**Methods::**

This clinical trial is designed to be conducted on 100 children aged 3 to 12 years for 12 weeks (Trial registration code: KCT0007386). We will evaluate changes in height, height percentile, standard deviation score of height, weight, body mass index, waist circumference, hip circumference, bone age, predicted adult height estimated by bone age, human growth hormone level, insulin-like growth factor-1 (IGF-1) level, IGF-binding protein-3 (IGFBP-3) level, IGF-1/IGFBP-3 ratio, and estradiol level. Additionally, we also will evaluate the adverse events during the study.

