**Figure 2. F2:**
[figure not shown]
Schedule of enrollment, intervention, and assessments. (a) Height, weight, and waist and hip circumference. (b) Hematologic and Serum Chemistry test, Urine test, Hormone test, Estradiol. * Researchers will record the dining pattern of the day before using the 24-h recall method. Additionally, researchers will withdraw and check the dietary questionnaire handed out during the previous visit. ** If there was an examination within 4 weeks, it can be used.

If it is determined that the number of study participants does not meet the expectations, changes or additions to the recruitment method will be implemented through discussion between the research sponsor, the person in charge, and the practitioner.

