##### 2.9..2..5. Height standard deviation score (SDS) and height SDS for BA.

The height SDS will be calculated by subtracting the average height of the same age and sex from the measured height of the participants and dividing the value by the standard deviation of the height. Accordingly, the height SDS for bone age and the height SDS for chronological age will be calculated based on bone age and chronologic age, respectively.

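### Section 2.9.2.4 lists bone age and predicted adult height at 6 and 12 weeks but not at baseline, which does not fit the changes announced in the abstract

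*Protocol article*

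**What the plan says.** Section 2.9.2.4 sets the times for two secondary outcomes: "BA and PAH will be measured at 6 and 12 weeks". It does not mention baseline.

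The Methods paragraph of the abstract opens its outcome list with "We will evaluate changes in height, height percentile, standard deviation score of height, weight, body mass index", and the same list goes on to "bone age, predicted adult height estimated by bone age". BA and PAH are therefore among the outcomes whose changes are to be evaluated. The reference time for those changes is not named.

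Section 2.9.2.5 adds an outcome that depends on BA: "the height SDS for bone age and the height SDS for chronological age will be calculated based on bone age" and chronological age, respectively. It gives no measurement times.

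The primary outcome shows the pattern used elsewhere: "Height and weight will be measured at baseline and at 6 and 12 weeks".

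Figure 2 is the schedule of assessments. The figure is not shown in the text at hand, but one of its notes reads: "If there was an examination within 4 weeks, it can be used". The visible text does not say which examination is meant.

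**The concern.** A change needs a reference value from before treatment. If both BA readings fall during treatment, any effect of the first six weeks is already in the reference and drops out of the week 6-to-12 difference. The Discussion says that BA and PAH are there to judge the effect on future growth, so the change since the start of treatment is the natural quantity.

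Two other parts of the plan lean on the same missing reading:

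- Section 2.10 carries the last observation forward for dropouts. A child who leaves before week 6 would have no BA or PAH value to carry.
- Section 2.9.2.4 chooses the PAH method partly by bone age, and section 2.10 sub-analyses PAH by method. If BA is first read at week 6, those subgroups are formed after treatment has begun.

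A baseline reading cannot be recovered once a child has been dosed.

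**Working it through.** **Step 1. Stated times side by side (protocol article).**

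| Outcome | Section | Baseline | Week 6 | Week 12 |
|---|---|---|---|---|
| Height, weight | 2.9.1 | yes | yes | yes |
| Height percentile | 2.9.2.2 | yes | yes | yes |
| Waist, hip circumference | 2.9.2.3 | yes | yes | yes |
| Hormones | 2.9.2.6 | yes | yes | yes |
| BA, PAH | 2.9.2.4 | not named | yes | yes |
| Height SDS for bone age | 2.9.2.5 | no times given | | |

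BA and PAH are the only timed outcomes without baseline. No other visible sentence supplies it.

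**Step 2. What the stated times allow.** For BA, PAH and height SDS for bone age, two quantities can be formed: the week 6-to-12 change, and the level at week 12 (or week 6).

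**Step 3. The plan's own sample size, for the number per arm.** Section 2.4 uses a difference of 1.35 cm, SD 2.0, two-sided 5% and 80% power. n = 2 × (1.960 + 0.842)² × (2.0/1.35)² = 34.5, rounded up to 35 per group. Then 35/0.7 = 50 per group, 100 in total. The figure reproduces. It concerns height and does not depend on BA.

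**Step 4. Precision of a raw week-12 comparison of BA.** The documents give no SD for BA. Assume ages uniform over a ten-year span (age 3 up to the 13th birthday) and BA spread equal to age spread. SE = SD × √(2/35) = SD × 0.239.

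- Unadjusted: SD = 10/√12 = 2.89 years, so SE = 0.69 year. With a nine-year span, SD = 9/√12 = 2.60 and SE = 0.62.
- Adjusted for the four strata of Table 1, as in the ANCOVA of section 2.10. Girls' strata are 6 and 4 years wide: 0.6 × 36/12 + 0.4 × 16/12 = 2.33. Boys' strata are 7 and 3 years wide: 0.7 × 49/12 + 0.3 × 9/12 = 3.08. With equal numbers of each sex the mean variance is 2.71, SD = 1.65 and SE = 0.39 year. A nine-year span gives nearly the same: girls 2.25, boys 3.25, mean 2.75, SD 1.66, SE 0.40.
- With all 50 per arm the multiplier is √(2/50) = 0.20, so SE = 0.58 unadjusted and 0.33 adjusted.

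The yardstick is a normal advance of one bone-age year per calendar year: 12/52 = 0.23 year over the trial. At 35 per arm the unadjusted SE is 0.69/0.23 = 3.0 times that, and the adjusted SE 0.39/0.23 = 1.7 times. A product that doubled the rate of bone maturation would shift BA by 0.23 year, only about 0.6 of the adjusted SE.

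**Step 5. The week 6-to-12 change.** The normal advance in that window is 6/52 = 0.115 year, half of 0.23. If an effect builds up linearly, half of it is seen. If the SD of the six-week change also equals that of the 12-week change, equal power needs 1/0.5² = 4 times the sample. Neither condition can be checked from the documents.

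**Step 6. Change from baseline.** The SD of a 12-week BA change is not given either. An assumed 0.4 year gives SE = 0.10; half and double that value give 0.05 and 0.19. The comparison of changes is more precise than the stratum-adjusted raw comparison for any change SD below 1.65 years.

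**The case against.** The strongest reply is that one sentence in a condensed article is not the schedule. Section 2.9.2.4 does not say that its two times are the only ones. The schedule is Figure 2, which cannot be seen here, and its four-week note shows that some examination near entry was planned. That could well be a screening bone-age reading, with baseline simply left out of the sentence. This stands. A reader might infer that the trial has no baseline BA and that the announced changes cannot be calculated; the documents do not support that.

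Other parts of the reply also stand:

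- Randomised groups can be compared on week-12 values without bias. What is lost is precision, not validity.
- The 0.69-year SE takes no account of the planned stratification adjustment; 0.39 is the fairer figure. Adjusting for chronological age, or analysing BA minus chronological age, would reduce it further, but section 2.10 names only stratification as covariate.
- The abstract lists the SDS of height, not height SDS for bone age, so a promised change in the latter is an inference.
- A reader might also take BA as a check on accelerated maturation. The Discussion ties its concern about precocious puberty to estradiol, which has a baseline.

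The reply does not remove the mismatch. The article gives times for its other measured outcomes and names baseline for each, so this is a stated schedule that disagrees with the stated outcome, not detail left to a fuller document.

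**Conclusion.** The point holds as an inconsistency to be reconciled. The times stated for BA and PAH omit baseline and do not fit the changes announced in the abstract. On those times alone, the analysis is confined to an on-treatment change or to a comparison of levels whose SE for BA is about 0.4 to 0.7 year at 35 per arm, against a 12-week advance of about 0.23 year.

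Those SEs rest on uniform ages over ten years, BA spread equal to age spread and, for the lower figure, equal numbers of girls and boys. They apply to BA only. PAH and height SDS for bone age are on other scales, and the documents give no SD for them.

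Whether a baseline reading is planned cannot be settled from the visible text. Either way section 2.9.2.4 needs correcting: if the reading exists, the section misstates the schedule; if not, the change since the start of treatment is unobtainable. The damage is limited to secondary outcomes. Height has a stated baseline, and the sample size is untouched.

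**What to change.** Check section 2.9.2.4 against Figure 2 and make them agree. State that BA and PAH are assessed at baseline (screening) and at 12 weeks, and define the outcome as change from baseline compared between groups. Give height SDS for bone age the same times.

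- If Figure 2 already has baseline, week 6 and week 12, keep all three and correct the sentence. This costs only a wording change.
- If only two readings are planned, take the first at baseline instead of week 6. The number of readings does not rise; the price is the loss of the interim reading.

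The note to Figure 2 should say which examination may be replaced by one from the preceding four weeks. If that is the bone-age examination, the note defines the baseline value. The change should be settled before dosing.

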##### 2.9..2..5. Height standard deviation score (SDS) and height SDS for BA.

The height SDS will be calculated by subtracting the average height of the same age and sex from the measured height of the participants and dividing the value by the standard deviation of the height. Accordingly, the height SDS for bone age and the height SDS for chronological age will be calculated based on bone age and chronologic age, respectively.

##### 2.9..2..6. Insulin-like growth factor-1 (IGF-1), insulin-like growth factor-binding protein-3 (IGFBP-3), IGF-1/IGFBP-3 ratio, estradiol, and human growth hormone.

A total of four hormones including human growth hormone, IGF-1, IGFBP-3, and estradiol, are selected as indicators to determine the participants’ height growth status. Levels of these hormones will be measured via blood tests at baseline and 6 and 12 weeks to determine the amount of change after using antler extract. Blood collected for laboratory testing (human material) is collected and managed in the hospital, and is discarded immediately after analysis for clinical research. Secondary use does not apply.

### 2.10. Statistical analyses

In this study, analysis will be performed by defining the analysis group as safety, full analysis set (FAS), and per-protocol set analysis. The safety analysis group will be defined as all subjects who have been randomized and who have consumed at least 1 study food and will be evaluated for safety. The FAS analysis group refers to subjects for whom data on primary outcomes can be obtained among those who have taken research food at least once. The per protocol set analysis group includes subjects who have completed the study without serious violations (violation of inclusion and exclusion criteria, use of concomitant medications that are not permitted, and medication adherence less than 70%) according to the research protocol among subjects included in the FAS analysis group. If missing data occurs during FAS analysis or if a subject drops out before the clinical study is terminated, data analysis will be performed with the most recently obtained data as if it were obtained at that time (Last Observation Carried Forward Method).

Statistical analysis is intended to test whether there is a statistical difference between the test and control groups. Therefore, the mean, standard deviation, median, minimum, and maximum values of the outcome measurements will be calculated, and comparisons between the groups will be performed using a 2-sample t-test (Wilcoxon’s rank sum test when the assumption of normality distribution is not satisfied). For laboratory tests and vital sign results, a paired t-test will be used to analyze whether there will be a difference in the amount of change within the group at the end of administration of the test substance compared with before treatment (screening). Further, PAH will be sub-analyzed according to calculation methods such as the VunoMed, TW, and growth chart methods. Additionally, covariate analysis (analysis of covariance; ANCOVA) with stratification as a covariate and subgroup analysis for each stratification will be conducted.

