### 2.3. Participants

One hundred children from the Kyung Hee University Medical Center will be recruited. The study will be advertised using posters and banners announcing the need for volunteer participants. The participants and their guardians will receive research information, such as objectives, procedures, and potential benefits and harms, through standardized dialogue. Informed consent will be obtained from the children and their guardians before the screening process. Participants are allowed to withdraw from the study at any time. The research procedure will be conducted as shown in Figures 1 and 2.

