### 2.4. Sample size

The expected difference in height change was set to 0.45 cm.^[14]^ Based on this, the difference between groups was tripled and set at 1.35 cm. The standard deviation (σ) was set to 2.0, which is the standard for growth disorders (less than −2.0 standard deviation from the average of children of the same age and sex). Accordingly, the sample size was calculated using a 2-tailed 5% significance level, 80% power, and a 1:1 allocation. Accordingly, the required number of subjects per group is 35 and the total number of enrolled subjects is 100 (50 in each group), allowing for a 30% withdrawal rate.

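### Children who drop out are analysed on an earlier, predictably too low height, and the plan does not say that those who stop the study food are still measured at week 12

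*Protocol article*

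**What the plan says.** Section 2.4 enrols 50 children per group so that 35 remain, "allowing for a 30% withdrawal rate". Section 2.3 adds: "Participants are allowed to withdraw from the study at any time". Section 2.9 (primary outcome) has height taken barefoot on a portable stadiometer at baseline, week 6 and week 12.

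For children who leave, section 2.10 gives one rule for the full analysis set (FAS), last observation carried forward: "if a subject drops out before the clinical study is terminated, data analysis will be performed with the most recently obtained data". Membership of that set is defined in the same section: "The FAS analysis group refers to subjects for whom data on primary outcomes can be obtained among those who have taken research food at least" (a single intake suffices). The per-protocol set then removes, among others, children with adherence below 70%.

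The article does not say whether a child who stops the study food, but whose family would still come, is measured at week 6 or week 12. It neither plans this nor rules it out.

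**The concern.** Carrying a value forward assumes that nothing changes after the last visit. That cannot be true of height in children aged 3 to 12. Section 3 itself says that at least 95% of children grow faster than 4 cm/year. With three height visits, the carried value can only be week 6, or baseline for a child who left before week 6 and is nevertheless admitted to the FAS. Either is predictably too low as a week-12 height.

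The error need not be equal in the two arms. Children who stop because of taste, adverse events or disappointing growth are not a random subset. If one arm loses more children, its mean height change is pulled down for a reason unrelated to the product. More losses on placebo would look like a benefit, and more losses on antler extract would hide one.

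The true value is often cheap to get. It is one non-invasive reading at a visit that is already scheduled, and it stays meaningful in a child no longer taking the food.

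**Working it through.** **Inputs.** From section 2.4: "using a 2-tailed 5% significance level, 80% power, and a 1:1 allocation"; "the difference between groups was tripled and set at 1.35 cm" (from 0.45 cm); "The standard deviation (σ) was set to 2.0"; "the required number of subjects per group is 35"; 30% withdrawal. From section 2.9: height at weeks 0, 6 and 12. From section 3: growth above 4 cm/year in at least 95% of children. The 1.35 cm and the SD of 2.0 (read as cm) are taken as given here.

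**1. The plan's own figures.** n per group = 2 × [2.0 × (1.960 + 0.842) / 1.35]² = 34.45, rounded up to 35. Enrolment: 35 / 0.70 = 50 per group. Budgeted withdrawals: 0.30 × 50 = 15 per group. The stated sample size reproduces.

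**2. Growth missing from a carried height, at the 4 cm/year floor.**
- Week 6 carried: 4 × 6/52 = 0.46 cm.
- Baseline carried: 4 × 12/52 = 0.92 cm.

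For children growing faster than the floor, the shortfall is larger.

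**3. Unequal dropout, no true effect.** Assumption: 40% leave one arm and 20% the other. The article gives only a single 30% rate. Artefact = (difference in dropout) × (missing growth).
- Week 6 carried: 0.20 × 0.46 = 0.09 cm.
- Baseline carried: 0.20 × 0.92 = 0.18 cm.

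Against 1.35 cm this is 7% to 14%. Against the 0.45 cm from the cited source it is 20% to 41%. With a milder assumed split of 35% versus 25%, the figures halve to 0.05 and 0.09 cm. With equal dropout the artefact is zero.

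**4. Equal 30% dropout, true difference 1.35 cm.** Assumptions: growth and effect are linear over 12 weeks and the SD stays 2.0. A child carried from week 6 contributes half the effect, and one carried from baseline contributes none. Expected difference = 1.35 × (0.70 + 0.30 × c), where c is the average share of the effect carried. Power = Φ(difference / (2.0 × √(2/50)) − 1.960).

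| Value carried | c | Expected difference | Power, 50 per group |
|---|---|---|---|
| All week 6 | 0.50 | 1.15 cm | 82% |
| Half week 6, half baseline | 0.25 | 1.05 cm | 74% |
| All baseline | 0 | 0.95 cm | 66% |

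For reference, 35 per group with the full 1.35 cm gives 81% by the same formula.

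**5. If all 50 per group were measured at week 12.** Power for 1.35 cm would be 92%. This is an upper bound, because it requires children who stop to keep the whole effect and every family to agree. At the other extreme, suppose a child who stops exactly at week 6 keeps the gain so far and gains nothing more from the product. The true difference is then also 1.35 × (0.70 + 0.30 × 0.50) = 1.15 cm. In that case measurement does not enlarge the difference. What it removes is the missing background growth, and with it the artefact in step 3.

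**The case against.** A reader might infer that the plan gives up the week-12 height of every child who stops the product, and that up to 15 obtainable heights per group are thrown away. The text does not support that. The rule in section 2.10 concerns children who drop out, and section 2.3 speaks of leaving the study. Neither says that a child who merely stops the food is no longer measured. A journal article may leave such procedures to the full protocol. The adherence clause also points the other way: children below 70% are removed only from the per-protocol set, so poor takers can remain in the FAS with measured heights. The 15 per group is a sample-size allowance and therefore a ceiling, and it includes families who withdraw consent and cannot be measured.

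The size is open to challenge too. The 0.09 to 0.18 cm is a product of carry-forward under an assumed split. The upper figure needs baseline to be carried, yet the FAS definition may exclude a child with no post-baseline height, in which case 0.18 cm does not arise. Nor are missing heights beyond all repair: with a week-6 value, likelihood-based or imputation methods are valid if data are missing at random.

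All of this stands and limits the claim. It does not remove the point. The article does fix a rule for those who leave, that rule gives values known to be too low, and nothing in it directs that a measured height be sought first.

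**Conclusion.** The point holds as a recommended improvement. It does not show that the plan excludes measurement after stopping. The plan budgets for up to 15 of 50 withdrawals per group, and its only stated rule for those who drop out substitutes a height short by at least about 0.46 cm (week 6) or 0.92 cm (baseline, if such a child is analysed at all) for the 95% or more of children growing above the stated floor.

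The between-arm bias depends wholly on unequal dropout, and its size rests on the assumed 40% versus 20% split. Under equal dropout what remains is a shrunken expected difference, by 15% to 30%, given linear growth and effect. Part or all of that shrinkage could be real if the effect ends when the food is stopped. The case for measuring is therefore an observed, less biased comparison of the randomised groups, with any gain in power uncertain.

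**What to change.** In sections 2.3 and 2.10:

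- Separate stopping the study food from withdrawing consent to the study.
- State that every child who stops the food, for any reason, is asked to attend the scheduled week-6 and week-12 height measurements where consent allows. Families who decline full visits can be asked for the week-12 height alone.
- Use those measured heights in the FAS in place of a carried value.
- Limit the missing-data method to children who cannot be measured. For them, a mixed model for repeated measures or multiple imputation, with sensitivity analyses, suits a rising outcome better than carry-forward.
- Say whether a child with no post-baseline height belongs to the FAS.

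If the full protocol already provides for these measurements, section 2.10 need only say so and give the measured height precedence. No rule on when a child stops the food is affected.

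The cost is small: protocol and consent wording, and a short non-invasive reading at existing visits. The downside is that off-product heights may dilute the estimate and need not restore 1.35 cm. The per-protocol set still shows the on-product effect.

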Deer antlers are cut and dried young male antlers of Cervus nippon Temminck (梅花鹿), Cervus elaphus Linne (馬鹿), or Cervus canadensis Erxleben (大鹿) and are the fastest growing part of the animal tissues. Insulin-like growth factor-1 (IGF-1), which promotes bone growth, is produced in growing deer antlers, and IGF-1 is known to play an important role in the metabolism of osteoblasts that grow bones. Deer antler is originally a representative tonifying yang medicine (補陽藥) and has effects such as tonifying kidney yang (補腎阳), replenishing essence and blood (益精血), and strengthening muscle and bone (强筋骨).^[20]^ Kidney yang (腎阳) activates overall physiological function by warming the organs of the human body. Based on the efficacy of antlers, this clinical study is designed to prove the safety and effectiveness of promoting height and growth in children and adolescents.

The primary outcome item, height change, is the most intuitive item for judging a child’s growth. Generally, children older than 2 years whose height velocity is less than 4 cm/year should be monitored carefully for chronic nutritional deficits or other causes of short stature because at least 95% of children grow faster than 4 cm/year.^[21]^ However, since each subject’s current growth status is different, items such as SDS and height percentile are selected as secondary outcome measurements. In addition, since length growth is not the only growth indicator, weight growth-related indicators such as weight, waist circumference, and hip circumference will be also measured. Further, to determine the effect on future growth, bone age and predicted adult height will be used for growth prediction.

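### Last observation carried forward (LOCF) for the full analysis set gives dropouts too little growth: it shrinks a true height effect and, if dropout is unequal, favours the better-retained arm

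*Protocol article*

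**What the plan says.** Section 2.10 (Statistical analyses) applies the rule broadly: "If missing data occurs during FAS analysis or if a subject drops out before the clinical study is terminated", then "data analysis will be performed with the most recently obtained data as if it were obtained at that time (Last Observation Carried Forward Method". It names no other method for missing data and no sensitivity analysis. It defines the full analysis set (FAS) as "subjects for whom data on primary outcomes can be obtained among those who have taken research food at least once". It does not say whether a height after baseline is needed. The per-protocol set is limited to FAS children who completed the study without serious violations.

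The Discussion identifies the primary outcome: "The primary outcome item, height change, is the most intuitive item for judging a child’s growth". Section 2.9 gives the measurement times: "Height and weight will be measured at baseline and at 6 and 12 weeks". The Discussion also states that "at least 95% of children grow faster than 4 cm/year". Section 2.4 (Sample size) says "The expected difference in height change was set to 0.45 cm", triples this to a design difference of 1.35 cm with an SD of 2.0, and enrols 100 children, "allowing for a 30% withdrawal rate".

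**The concern.** LOCF supposes that the outcome stays where it was when the child left. Height in children aged 3 to 12 does not, and the protocol's own growth figure says so. A carried week-6 height credits a child with about half of the 12-week growth; a carried baseline height credits none. The error has a known direction for each affected child and is as large as the effect taken from the literature.

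Two results are at stake. If the extract works, the estimate is pulled toward zero. If one arm loses more children, its mean growth is pushed down and the other arm looks better, with or without an effect. The rule is fixed in the current text, so this is a stated choice and not a detail left to an analysis plan.

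**Working it through.** **Inputs from the article.** Heights at weeks 0, 6 and 12 (2.9); growth above 4 cm/year in at least 95% of children (Discussion); cited difference 0.45 cm, design difference 1.35 cm, SD 2.0, two-sided 5%, 80% power, 1:1, 30% withdrawal (2.4).

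**Assumptions.** Growth and any effect accrue evenly over the 12 weeks. Dropout is unrelated to growth. The split and timing of dropout are not in the article, and neither is the 6 cm/year used as an upper example.

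**The plan's own figure.** n per group = 2 × (1.960 + 0.842)² × 2.0² / 1.35² = 34.5, so 35; 35 / 0.70 = 50 per group, 100 in all. This reproduces. The allowance corresponds to up to 0.30 × 50 = 15 children per arm.

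**Growth lost per child at 4 cm/year.**
- Week-6 height carried: 4 × 6/52 = 0.46 cm.
- Baseline height carried: 4 × 12/52 = 0.92 cm. This arises only if the FAS keeps children with no later height.

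**Equal dropout d, true difference D.** Expected LOCF difference = D × (1 − d × share of growth lost). With d = 0.30:
- Week 6 carried (share 0.5): 0.45 × 0.85 = 0.38 cm; 1.35 × 0.85 = 1.15 cm. Loss of 15%.
- Baseline carried (share 1): 0.45 × 0.70 = 0.315 cm; 1.35 × 0.70 = 0.945 cm. Loss of 30%.

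**Unequal dropout, no true effect.** False difference = 12-week growth × share lost × difference in dropout. Twelve-week growth is 0.92 cm at 4 cm/year and 6 × 12/52 = 1.38 cm at 6 cm/year.

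| Dropout in the two arms | Carried height | 4 cm/year | 6 cm/year |
|---|---|---|---|
| 30% / 30% | either | 0 | 0 |
| 35% / 25% | week 6 | 0.05 cm | 0.07 cm |
| 40% / 20% | week 6 | 0.09 cm | 0.14 cm |
| 40% / 20% | baseline | 0.18 cm | 0.28 cm |

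The week-6 figures for 40%/20% are 21% and 31% of 0.45 cm, or 7% and 10% of 1.35 cm. The sign follows whichever arm keeps more children.

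**Type I error.** Simulated with 50 per arm, 6 cm/year, week-6 carry and dropout at random within each arm:

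| SD of 12-week growth | 35% / 25% | 40% / 20% |
|---|---|---|
| 0.35 cm (plus 0.3 cm reading error) | about 9% | about 19–21% |
| 1.0 cm | 6.5% | 11% |
| 2.0 cm (stated SD, no reading error) | 5.4% | 6.9% |

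At equal 30% dropout and SD 0.35 cm, type I error is about 5%. A completers-only t-test also stays near 5%.

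**Power at equal 30% dropout.** With SD 0.35 cm and a 0.45 cm effect, LOCF has 84% against 92% for completers. With SD 2.0 and 1.35 cm, the order reverses: 88% against 79%.

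**The case against.** The best defence is that harm needs conditions the article does not predict. The trial is described as double-blind, it lasts 12 weeks, and the placebo is given in the same way, so dropout may well be similar in the two arms. With similar dropout there is no bias under the null, and a true effect is understated, which is conservative. The 30% is a planning allowance and not a forecast. The FAS wording can be read as requiring a height after baseline, which would remove the baseline-carry case. All this stands, and it limits the point to the conditional form given here.

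A reader might infer that LOCF always biases the comparison, or that it inflates the false-positive rate to 20% and costs power. The article does not support either. The large inflation needs both a lopsided split and a growth SD of about 0.35 cm, neither of which is in the text. At the stated SD of 2.0 the inflation is negligible and LOCF has more power than completers. That SD is itself taken from a cut-off for growth disorders, not from data on 12-week growth, so only a range is defensible.

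A reader might also infer that height SDS and percentile must fall falsely. That happens only if an old height is rescored at the week-12 age; carrying the recorded score forward causes no such fall, and the text does not say which is done.

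The per-protocol set contains no dropouts and gives a partial check. It does not correct the FAS result, and it is not protected if dropout is related to growth.

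**Conclusion.** The point holds in this conditional form. LOCF gives at least 95% of children last seen at week 6 a 12-week height that is too low by at least about 0.46 cm, on the protocol's own growth figure. At equal 30% dropout after week 6, a true effect is understated by about 15%. With unequal dropout a false difference favours the better-retained arm, about 0.09 to 0.14 cm for an assumed 40%/20% split at 4 to 6 cm/year. With no effect and equal dropout the bias is zero.

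These figures rest on even growth, on dropout unrelated to growth, and on a target difference that supposes all children had stayed on their product. The bias in the estimate does not depend on the SD. The consequences for type I error and power do, and the article has no data that settle them. The baseline-carry figures apply only if the FAS keeps children with no later height.

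**What to change.** Replace the LOCF sentence in section 2.10. Suggested content: the primary FAS analysis is a likelihood-based repeated-measures model of height change at weeks 6 and 12, with treatment, visit, treatment-by-visit, stratum and baseline height; the estimate of interest is the week-12 difference; observed heights are used without carrying forward. ANCOVA with multiple imputation from baseline height, week-6 height and stratum would serve equally well. Add one sensitivity analysis for data not missing at random. State whether the FAS requires a height after baseline. Do not carry forward height or the other growth measures.

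The cost is wording and modest programming, to be settled before unblinding. The downside is a missing-at-random assumption, which the sensitivity analysis is there to test. The heights are already scheduled, and the 100 children already allow for 30% loss, so neither visits nor sample size change on this account.
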